### 2.3. Design

The current study will employ a 24-week 2 × 2 crossover design. Participants will complete two 8-week dietary interventions, separated by an 8-week washout period. Participants will be allocated to a starting diet group, either the Mediterranean diet or the low-fat diet, using block randomisation and stratification based on age and gender. In Phase 1, participants will follow their starting diet for 8 weeks. All participants will then return to their habitual diet for 8 weeks, after which they will “cross-over” and complete the second 8-week intervention for Phase 2 (see Figure 1). All participants will therefore complete each experimental condition. 

The crossover design has been chosen for time and resource efficiency. As participants will act as their own control, potential differences between subjects in both observed and unobserved confounders that may be present in a medium-sized parallel-group design will be removed. This will reduce the potential for bias in estimating the treatment effect. In addition, repeat measures on the same individual allows for separate estimation of the true underlying value for each individual, the treatment effect and the measurement error. Separating the treatment effect from the measurement error will allow a more precise estimation of the treatment effect and fewer participants will therefore be required to detect any between-group differences. The reduced bias due to the removal of potential confounding variables will also enhance the internal validity of the design. An 8-week intervention period is expected to be adequate as similarly timed RCTs have demonstrated significant effects of nutrients contained in the Mediterranean diet, such as flavanols and omega-3s, on cardiovascular outcomes [46,48,121]. Further, the observed changes in cardiovascular outcomes were found to mediate improvements in cognitive function. As there is the potential for latency effects beyond 8 weeks, Potential carry-over effects will be assessed by testing for treatment × phase interactions, and it is anticipated that 8 weeks will be an adequate washout period to prevent cross-contamination between intervention phases [109]. Practice effects of cognitive tasks will be mitigated through the use of measures with strong test-retest reliabilities, counterbalancing of test order and the use of multi-level analysis that will allow the separation of measurement error (i.e., within-subject variability) from treatment effects.

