### 2.5. Outcomes

#### 2.5.1. Blood Pressure

Home measured systolic blood pressure will be the primary outcome. Home blood pressure assessments have stronger predictive power for complications of hypertension and mortality than clinic blood pressure assessments [127,128]. Further, multiple home blood pressure measurements have comparable reliability to ambulatory blood pressure measurements in evaluating hypertension [129]. Participants will be provided with an A&D Company Ltd. digital blood pressure monitor (model UA-767) and instructed to measure their blood pressure and heart rate every morning, afternoon and evening, for a period of six days at each of the four study time-points. Participants will be asked to take measurements at consistent times each day, at least one hour after the consumption of caffeine or alcohol and 30 min after food or exercise. Each measurement of blood pressure will follow a five-minute resting period in the seated position and three readings will be taken, spaced at least one minute apart [130,131]. Home blood pressure will be recorded at four time-points over the course of the trial, one week prior to clinic assessment visits (at pre-baseline, Week 7, Week 15 and Week 23). Blood pressure will also be measured in-clinic using an Omron Healthcare Co. digital blood pressure monitor (model 1A1B Hem-7000-CIL) at the beginning and end of each dietary phase. A similar protocol for in-clinic measurements will be used, with blood pressure and heart rate measurements following a five-minute resting period in the seated position. Three readings will be taken at each visit, spaced at least one minute apart.

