To analyse the difference between dietary interventions a linear mixed-effects analysis will be performed to measure both within and between subject effects for cardiometabolic and cognitive outcomes. Potential confounding variables including weight loss, changes to physical activity, medications or dietary supplements, carryover and period effects will be included in the analysis. Potential carryover effects and treatment-period effects will be assessed by adding treatment × phase and treatment × order interaction terms in the mixed effects analyses. We will also assess possible seasonal effects by including a term for treatment × season interaction in a secondary analysis with season coded as a binary variable for Autumn or Spring versus Winter or Summer. Diet × period × energy intake interaction terms will be used to determine whether there are any significant changes in diet (total energy intake, macronutrient intakea, micronutrient intakes including sodium, and fatty acid ratios) between the two diet phases. If a significant change is detected in cognitive function a hierarchical regression will be performed to determine the influence of cardiometabolic outcomes. All statistical analyses will be conducted using SPSS for Windows, version 21.0 (SPSS Inc., Chicago, IL, USA) and Stata (version 14.2, StataCorp, College Station, TX, USA). Data will be presented as means ± standard deviation (SD) for descriptive statistics and as means ± standard error (SEM) for reporting estimated effects. All tests will be 2-tailed and *p*-values < 0.05 will be deemed statistically significant.

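### The binary season coding pools seasons half a year apart, so the planned secondary check is blind or unreliable for an ordinary annual cycle

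*Protocol article*

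**What the plan says.** Section 2.7 states the purpose and the term: "We will also assess possible seasonal effects by including a term for treatment × season interaction in a secondary analysis". The same sentence fixes the variable: "season coded as a binary variable for Autumn or Spring versus Winter or Summer". No reason is given for this grouping, and season is mentioned nowhere else in the article.

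Three other statements give the context:
- Section 2.3: "The current study will employ a 24-week 2 × 2 crossover design", with two 8-week diet phases and an 8-week washout between them. Starting diet is allocated by block randomisation, stratified by age and gender.
- Section 2.5.1: "Home measured systolic blood pressure will be the primary outcome", recorded "at pre-baseline, Week 7, Week 15 and Week 23".
- Section 2.7: period effects are among the terms to be included in the mixed-effects analysis.

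**The concern.** Seasonal variation is usually pictured as one cycle a year, with its high and low points about six months apart. The coding puts winter with summer and autumn with spring, so each level holds two seasons whose deviations from the yearly mean are opposite in sign. A variable built this way averages out the pattern it would normally be expected to find.

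Season is relevant in this design because the two on-diet home readings (Weeks 7 and 23) are 16 weeks apart. A participant's two diets are therefore usually observed in different parts of the year. If the seasonal check finds nothing, a reader is likely to take that as evidence that season did not matter. At stake is whether this secondary analysis can support that statement.

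**Working it through.** The article gives no figure for the seasonal analysis, so there is nothing to reproduce. The check is of the coding itself.

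**Inputs.** The coding comes from section 2.7 and the measurement weeks from section 2.5.1. The shape of the seasonal effect is not given. I assume an annual cosine of amplitude A, four seasons of equal length, and any peak date.

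**Step 1: season means.** The mean of a cosine over the quarter-year centred on its peak is (2√2/π)A = 0.90A. With a mid-winter peak the means are winter +0.90A, spring 0, summer −0.90A, autumn 0.
- Winter minus summer: 0.90A − (−0.90A) = 1.80A.
- Planned contrast with equal shares: (0.90A − 0.90A)/2 − (0 + 0)/2 = 0.

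**Step 2: other peak dates.** Values half a year apart are always equal and opposite, so the result is general. Moving the peak by a tenth of a year gives winter +0.73A, spring +0.53A, summer −0.73A, autumn −0.53A. Both pooled means are again 0. The same algebra applies to the interaction: if the diet effect itself follows an annual cycle, its winter and summer deviations cancel within one level, and its autumn and spring deviations within the other.

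**Step 3: unequal shares.** Let p be winter's share of the winter/summer observations, with a mid-winter peak. The contrast is 0.90A·p − 0.90A·(1 − p) = 0.90A(2p − 1).

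| p | Coded contrast | True winter−summer difference |
|---|---|---|
| 50% | 0 | 1.80A |
| 60% | 0.18A | 1.80A |
| 75% | 0.45A | 1.80A |
| 100% | 0.90A | 1.80A |

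If summer predominates the sign reverses: p = 25% gives −0.45A. The coefficient thus follows the recruitment calendar as much as the seasonal effect.

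**Step 4: what the coding can detect.** For a half-yearly cycle of amplitude A, in which winter and summer move together, the means are +0.64A, −0.64A, +0.64A, −0.64A and the contrast is 1.27A. The coding suits an extreme-versus-mild hypothesis, which the article does not state.

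**Step 5: the primary comparison.** Over 16 weeks one person's seasonal shift is at most 2A·sin(π × 16/52) = 1.65A. Suppose, as an assumption, that winter and summer differ by 3 to 8 mmHg, so A = 3/1.80 to 8/1.80 = 1.67 to 4.44. Take year-round starts, the 31 participants required in section 2.7, and the standard crossover estimator, which is half the difference between the two orders in mean period difference. The seasonal error in the diet effect then has mean 0. Without blocking its SD is √[¼ × (1.65A)²/2 × (1/15 + 1/16)] = 0.21A, or about 0.35 to 0.93 mmHg. In simulation, a single sequence of blocks of 4 (block size assumed) reduces this to about 0.12 to 0.31 mmHg. Blocks of 4 within four strata (also assumed) give about 0.28 to 0.75 mmHg.

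**The case against.** Several points on the other side are sound.

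- **Complete cancellation is conditional.** A reader might infer that the check has no power at all. That holds only when opposite seasons are equally represented, and the article gives no recruitment calendar. With readings at Weeks 7 and 23, a mid-winter peak and assumed recruitment windows of 60, 120 and 180 days, the absolute contrast averaged over start dates is 0.73A, 0.44A and 0.29A. It is 0 for a full year. This stands, and it makes the coding unreliable rather than always blind. It does not make the coefficient interpretable, because its size and sign are then set by when people happened to enrol.
- **A season main effect is not ruled out.** A reader might infer that season enters only as an interaction. The sentence names the interaction and is silent on the main effect, which is ordinarily fitted alongside. Under this coding a main effect would have the same weakness.
- **The primary result is protected.** A reader might set a winter-summer swing of several mmHg against the 2.5 mmHg target in section 2.7 and infer bias of that order. The swing is not the error in the diet effect. Block randomisation tends to balance the orders over calendar time and period terms absorb the average shift between phases. What remains is chance imbalance with expectation zero, partly reflected in the standard error.
- **Extreme versus mild seasons is a testable hypothesis.** This is true, but the article does not put it forward. The stated aim is to assess "possible seasonal effects" in general.

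**Conclusion.** The point holds as a defect in a secondary analysis, of minor to moderate weight. As coded, the season variable loses all of an annual cycle when opposite seasons are equally represented. With a mid-winter peak, it still shows only 0.18A to 0.45A of a 1.80A winter-summer difference when winter's share is 60% to 75%. A null finding would not be evidence that seasonality is absent, and a positive one could not be separated from the recruitment pattern.

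This rests on an annual cycle and seasons of equal length. The zero contrast holds for any peak date, while the partial figures are for a mid-winter peak. The primary diet comparison, its model and its sample size do not depend on this variable and are not invalidated.

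**What to change.** In the secondary model of section 2.7, derive season from the calendar date of each measurement and enter it as sine and cosine of day of year. Alternatively, use a factor that keeps winter and summer apart, such as four levels. State that the main effect is included together with its interaction with diet. A two-level cool-versus-warm split is a weaker substitute: it gives 0.90A for a mid-winter peak but 0 when the peak falls on the winter-spring boundary. If extreme versus mild seasons is the intended hypothesis, the article should say so and give the reason.

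The cost is a sentence of analysis text, use of the visit or measurement dates, and some degrees of freedom. The binary coding with its main effect uses 1 + 1 = 2 terms. Sine and cosine use 2 + 2 = 4, which is two more. A four-level factor uses 3 + 3 = 6, which is four more and less comfortable with 31 to 40 participants.

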Consistent with Australian Dietary Guidelines [75], serving sizes of dairy foods will deliver 300 mg of calcium. Three to four servings of dairy each day will therefore provide approximately 900 to 1200 mg of calcium, while vegetables and nuts will provide approximately 100 mg. Based on this modelling, the MedD diet will provide 1000–1300 mg of calcium each day, and thus meet the Australian RDI for calcium.

Although recommended for the control of blood pressure, restriction of dietary sodium is not a component of the Mediterranean diet and thus participants will not be instructed to reduce salt intake. 

To assist with adherence, the following foods will be provided: Chobani Greek yoghurt (donated by Chobani Australia Pty Ltd., Dandenong South, Victoria, Australia), almonds (donated by the Almond Board of Australia, Loxton, Australia), walnuts and hazelnuts, EVOO (donated by Cobram Estate, Southbank, Victoria, Australia), Mainland Tasty regular fat and reduced fat cheese slices (donated by Fonterra Co-Operative Group, Darnum, Victoria, Australi), Edgell chickpeas, cannellini beans, red kidney beans, 4-bean mix and lentils (donated by Simplot Australia Pty Ltd., Rose Park, Australia) and canned John West tuna “tempters” and salmon “tempters” (donated by Simplot Australia Pty Ltd.). 

Adverse effects of the Mediterranean diet may include constipation, diarrhoea and bloating due to a high intake of fibre. Participants will be encouraged to discuss any adverse effects during dietetic counselling sessions, in which the dietitian will offer advice to minimise discomfort. 

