##### Diet Adherence

Adherence to the MedD intervention will be assessed using the weekly checklist (Appendix C, described above). Weekly totals of each food group will be compared against dietary guidelines to determine % adherence to the MedD diet. A 14-item Mediterranean diet adherence tool, adapted from the PREDIMED study to align with the Australian food supply and The Australian National Health and Medical Research Council (NHMRC) guidelines for alcohol consumption, will also be completed and returned at each fortnightly visit [61] (Appendix F). Adherence to the LFD will be measured using a 9-item low-fat diet adherence tool adapted from the PREDIMED study, completed and returned at each fortnightly visit [61] (Appendix G). These tools are designed to capture a generalised pattern of consumption relevant to the dietary phase. Finally, a 6-day weighed food record (WFR) will be completed before and during each dietary phase to calculate energy and macro and micronutrients intakes. 

Adherence to the whole dietary phase and the dairy food component of the MedD intervention will be determined at the first fortnight dietetic visit. Participants must meet a minimum of 75% adherence (as determined by checklists) to the relevant dietary prescription and a minimum of 75% adherence to the dairy recommendation (i.e., participants need to consume at least 3 serves dairy products per day to be compliant). If participants are unable to increase adherence above 75% in the next fortnight they will be excluded from the study.

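### The Diet × period × energy intake interaction named to test for intake changes between the diet phases does not estimate a between-diet difference in intake

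*Protocol article*

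**What the plan says.** Section 2.7 (Power Calculation and Statistical Analyses) gives one analysis for the dietary intake data: "Diet × period × energy intake interaction terms will be used to determine whether there are any significant changes in diet". A bracketed list then gives the intakes meant: total energy, macronutrients, "micronutrient intakes including sodium, and fatty acid ratios) between the two diet phases".

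The main model in the same section is stated for other variables: "a linear mixed-effects analysis will be performed to measure both within and between subject effects for cardiometabolic and cognitive outcomes". Intake is not among them.

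On the design, section 2.3 says "The current study will employ a 24-week 2 × 2 crossover design". On the data, the Diet Adherence part of section 2.5.2 says that "a 6-day weighed food record (WFR) will be completed before and during each dietary phase to calculate energy and macro and micronutrients intakes".

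**The concern.** The stated question is whether mean intakes differ between the two diet phases. That needs intake as the dependent variable and diet as the tested effect. The sentence instead puts energy intake inside an interaction, on the predictor side. Read literally, such a coefficient describes how the relation of some unnamed outcome to energy intake varies by diet and period. It can be null when intakes differ widely, and non-null when mean intakes are equal.

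What is at stake is the description of what the two diets delivered. Both diets are eaten ad libitum (section 2.4). Section 2.4.2 acknowledges that sodium restriction is recommended for blood pressure control, yet "participants will not be instructed to reduce salt intake". The low-fat diet sets no dairy target (section 2.4.1). Readers of the blood pressure result will want the between-diet differences in sodium, energy and calcium, and the authors plainly meant to examine intake. The analysis they name would not supply those differences.

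**Working it through.** The article states no figure for this test, so there is none to reproduce. The check has three parts.

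**1. What the term is, algebraically.** Code diet as d = +1 (MedD) or −1 (low-fat), and study phase as p = +1 (first) or −1 (second).
- MedD first: (d, p) = (+1, +1), then (−1, −1), so d × p = +1 in both phases.
- Low-fat first: (−1, +1), then (+1, −1), so d × p = −1 in both phases.

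The product d × p is therefore constant within a person and equals the sequence. Diet × period is the sequence (carryover) contrast, and diet × period × energy is sequence × energy: a difference between the two sequences in the slope of an outcome on energy. Neither is a difference in mean intake between diets.

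**2. Simulation.** Inputs from section 2.7: N = 31, two-sided α = 0.05, and a clinical outcome with SD 14 and between-phase correlation 0.5. Assumed, because the article gives no values: mean energy intake 8.7 MJ, SD 2 MJ, within-person correlation 0.5, mean outcome 135, and no dependence of the outcome on energy. There were 2,000 replicates per scenario, so the Monte Carlo standard error at 5% is √(0.05 × 0.95 / 2000) ≈ 0.5 percentage points.

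| True diet difference in energy (MJ) | Diet × period × energy, clinical outcome | Diet × period (phase), intake as outcome | Diet effect, intake as outcome |
|---|---|---|---|
| 0 | 4.8% | 5.3% | 5.1% |
| 0.5 | 4.1% | 5.7% | 25.9% |
| 1 | 4.3% | 5.1% | 76.7% |
| 2 | 5.4% | 5.0% | 100% |

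Entries are rejection rates. The first two tests stay near α however large the true difference. Only the diet effect with intake as the outcome responds to it.

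A hand check on the last column: the variance of the within-person difference is 2 × 2² × (1 − 0.5) = 4, so SE = √(4/31) = 0.36 MJ. A 1 MJ difference is then 1/0.36 ≈ 2.8 standard errors, in line with about 77% power.

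**3. Is the test stated elsewhere?**
- The mixed model in section 2.7 names cardiometabolic and cognitive outcomes only.
- The t-tests and chi-squared tests there compare completers with withdrawals at baseline, not the diets.
- The Diet Adherence part scores each diet with its own tool or against its own targets, for example "Weekly totals of each food group will be compared against dietary guidelines to determine % adherence to the MedD diet". It also derives a 15-point score from the food records. It states no between-diet test of nutrient intake.

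**The case against.** **The sentence may just be garbled.** The bracketed list could be read as naming the dependent variables, and a slip is likelier than a plan to regress an unnamed outcome on energy. That may well be the intention. Even so, energy intake remains in the term. For energy the test is then circular; for the other nutrients it examines modification by energy.

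**Period may mean before versus during a phase.** Food records are taken at both times, so diet × period with intake as outcome would be the between-diet difference in change, which is a sensible contrast. Under the same assumptions the per-person variance is 4 × 2² × (1 − 0.5) = 8 and SE = √(8/31) = 0.51 MJ. Rejection is then about 5%, 15%, 48% and 97% at 0, 0.5, 1 and 2 MJ. This shows that the defect depends in part on the reading. But section 2.7 uses period effects in the usual crossover sense, the sentence speaks of change between the two diet phases, and energy intake is still misplaced.

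**A condensed article leaves detail to an analysis plan.** True of omissions. Here a method is stated, and it does not fit its question.

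**A reader might infer that the dietary contrast goes untested, or that dairy delivery is unchecked.** The article does not support that. Each diet has its own adherence tool, participants must meet a dairy threshold stated as at least three serves a day, and dairy is scored from the food records at the same level.

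**A reader might also infer that sodium and energy are the main rival explanations for a blood pressure difference.** The article does not say so. The masking factor it names is weight loss, with weight measured fortnightly and weight change adjusted for. Intake differences arising under the randomised diets are part of each diet's effect and bear on mechanism, not on the validity of the diet comparison.

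**Conclusion.** The concern holds, in limited form. As worded, the named interaction does not estimate whether energy, nutrient, sodium or fatty acid intake differed between diets, and the article states no other valid between-diet test of these intakes. The algebra rests only on the 2 × 2 design and on period meaning study phase. The assumed SD and correlation set the power of the correct test, not this conclusion. The flat rejection rate of the three-way term assumes an outcome unrelated to energy; if the slope differed between sequences the term could be significant, but still not because mean intakes differ.

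The consequence is confined to describing the delivered dietary contrast. Intake and adherence are measured, and the primary blood pressure comparison is unaffected. It is worth correcting because the stated rule is wrong and easily put right.

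**What to change.** Replace the sentence in section 2.7 so that each weighed-food-record quantity (energy, macronutrients, sodium, calcium, fatty acid ratios) is the dependent variable in the crossover mixed model. Use fixed effects for diet, phase, order and pre-phase intake, and a random participant effect. Test the diet effect and report the between-diet difference with its 95% CI. Drop the three-way term.

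The food records are already planned before and during each phase, so the cost is one sentence and a little analysis work.

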### 2.7. Power Calculation and Statistical Analyses

In order to detect a clinically relevant difference of 2.5 mm Hg in the primary outcome measure of systolic home blood pressure with at least 90% power, a sample size of 31 volunteers is required. A reduction of 2.5 mm Hg in blood pressure translates to a risk reduction at a population level in stroke, hypertension and CVD of between 7% and 15% [133]. This calculation assumes a within-group standard deviation (SD) of 14 mmHg, a within-subject correlation between the 4 blood pressure measures at each visit of *r* = 0.6 based on previous studies [135,136], and a between-phase within-subject correlation of *ρ* = 0.5. This correlation (*ρ*) and the cross-over design reduces the number of required participants by a factor of (1 − *ρ*)/2 = 4 [153] i.e., from approximately *n* = 124 for a parallel group design using ANCOVA (*n* = 62 per group) to *n* = 31 subjects in total. To account for a withdrawal rate of 30%, an additional 9 volunteers will be recruited. 

To detect a statistically significant difference in *Z* scores for the cognitive outcomes Total Cognitive Functioning, Memory, Processing Speed and Executive Functioning, a sample size of *n* = 22 is required. This calculation assumes power equal to 0.8, an α level of 0.05, a correlation between measurements of 0.6, and a moderate effect size (Cohen’s *d* = 0.5) signifying a treatment effect of 0.5 SD [137]. A moderate effect size has been chosen on the basis of similar nutritional intervention studies that have detected significant improvements in cognitive outcomes, which may indicate restoration of cognitive function and reversal of cognitive decline [46,152].

Independent *t*-tests and chi-squared tests will be used to compare baseline demographic, cardiometabolic, cognitive, well-being and dietary characteristics between those who completed the study and those who withdrew.

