## 3. Discussion

Due to population ageing, the prevalence of illnesses such as CVD and dementia will continue to rise and the weight of their burden will be felt globally. Estimates suggest that delaying the onset of dementia by five years may reduce cost and prevalence by up to 44% [154,155]. Prophylactic measures endeavouring to reduce or delay the incidence of CVD and dementia therefore warrant thorough attention. 

Randomised controlled trials and cross-sectional investigations suggest that the Mediterranean diet may be effective for preventing both CVD and dementia. However, the Mediterranean diet is typically lower in dairy foods and calcium than Australian recommendations and long-term adherence may compromise health across the lifespan. The current paper outlines the protocol for a randomised controlled trial that will evaluate the impact of increased dairy intake in a Mediterranean dietary pattern to meet Australian recommendations for dairy foods and calcium. A comprehensive set of cardiovascular and cognitive outcomes will be measured to determine whether the Mediterranean diet with added dairy can significantly reduce CVD and dementia risk.

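### Four cognitive scores are each tested at 0.05 and none is named as decisive, so a chance cognitive difference arises about 10% to 16% of the time under assumed correlations, against 5% for one test

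*Protocol article*

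**What the plan says.** The protocol article names one primary outcome, home systolic blood pressure (Abstract, sections 1.4 and 2.5.1). Cognitive and cardiometabolic measures are labelled secondary (Abstract, sections 1.4 and 2.5.2).

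Section 2.7 then gives the cognitive question its own sample size. For a difference in Z scores on the "cognitive outcomes Total Cognitive Functioning, Memory, Processing Speed and Executive Functioning, a sample size of *n* = 22 is required". The inputs are stated once for all four scores: "This calculation assumes power equal to 0.8, an α level of 0.05, a correlation between measurements of 0.6". The effect size is described as moderate, "signifying a treatment effect of 0.5 SD". None of the four is singled out.

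The same section fixes one threshold for everything: "All tests will be 2-tailed and *p*-values < 0.05 will be deemed statistically significant". It also makes a later analysis depend on the cognitive result: "If a significant change is detected in cognitive function a hierarchical regression will be performed to determine the influence of cardiometabolic outcomes".

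Section 3 says what the results are for, naming the risk of dementia next to that of CVD (the quote stops just before it): "A comprehensive set of cardiovascular and cognitive outcomes will be measured to determine whether the Mediterranean diet with added dairy can significantly reduce CVD and".

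**The concern.** Cognition is more than descriptive background in this trial. It is a stated objective, it has its own power calculation, and the article plans to conclude on it. For such a question the plan should say which result decides it. Section 2.7 does not: four scores stand side by side, each is significant at p < 0.05, and as written a significant result on any of them counts as a change in cognitive function and starts the regression on cardiometabolic outcomes.

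With four chances instead of one, a difference on at least one score will appear by chance more often than the 0.05 attached to each test. At stake is a cognitive finding, and an analysis of its cardiovascular explanation built on it, resting on whichever score crossed the line. The article hopes that its findings may contribute to national dietary guidelines, so the reader should know in advance which score carries the claim.

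**Working it through.** **Inputs from section 2.7.** Four scores (Total, Memory, Processing Speed, Executive Functioning); two-sided p < 0.05 for each; d = 0.5; correlation between measurements 0.6; power 0.8; stated n = 22.

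**Inputs not in the document, assumed here.** The correlation between the three domain scores (taken from 0 to 0.8), and Total as the mean of the three domains.

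**1. The plan's own figure.** For a paired comparison the standardised difference is d / √(2(1 − r)) = 0.5 / √(2 × 0.4) = 0.559. With the noncentral t distribution, a one-sided alpha of 0.05 gives n = 22 (power 0.81). A two-sided alpha of 0.05 gives n = 28, and power 0.71 at n = 22. So 22 can be reproduced with an unadjusted 0.05 for each score. That the match is one-sided while section 2.7 says all tests are two-tailed is a separate matter. A two-sided route also reaches 22 (126 × 0.7 × 0.25 = 22.05), but only by borrowing the four-measure averaging and ρ = 0.5 of the blood pressure calculation. By either route, 0.05 is not divided among the four scores.

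**2. Independent scores.** P(at least one significant) = 1 − (1 − 0.05)^k.
- k = 4: 1 − 0.95⁴ = 0.185
- k = 3 (domains only): 1 − 0.95³ = 0.143

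**3. Correlated scores.** If Total is the mean of three domains with common correlation ρ, its correlation with each domain is √((1 + 2ρ)/3), for example 0.577 at ρ = 0 and 0.816 at ρ = 0.5. Two million draws of null z statistics were simulated at each ρ. The last two columns treat all four scores as equally correlated at ρ.

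| ρ | Three domains + Total: either direction | Three domains + Total: favourable only | Four equally correlated: either direction | Four equally correlated: favourable only |
|---|---|---|---|---|
| 0 | 16.1% | 8.2% | 18.5% | 9.6% |
| 0.3 | 14.5% | 7.2% | 17.4% | 8.7% |
| 0.5 | 12.9% | 6.5% | 15.6% | 7.8% |
| 0.6 | 12.1% | 6.0% | 14.4% | 7.2% |
| 0.8 | 9.9% | 5.0% | 11.4% | 5.7% |

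For one two-sided test the corresponding rates are 5% in either direction and 2.5% in the favourable direction.

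**4. What different repairs would cost.** At 31 completers, two-sided paired t, d = 0.5, r = 0.6:
- One key score at 0.05: error 5%, power 0.85, as now.
- Bonferroni over four scores (0.0125 each): error 4.9% if independent, power 0.67 per score, and 39 completers needed for 80%.
- Holm over the three domains, first step (0.05/3): power 0.72.

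**The case against.** The strongest reply is that this is a journal article, that handling of multiple secondary outcomes is usually left to the statistical analysis plan, and that the threshold sentence is a standard closing line. It gives a per-test threshold and nowhere promises 5% across a family. This stands in part: comparing a familywise rate with 5% does not show the plan breaking a promise. The point survives because the article is not silent. It sizes four co-equal scores at an unadjusted 0.05, applies one rule to all tests, and lets an unspecified cognitive result trigger a further analysis. An analysis plan that named a decisive score would have to narrow that rule.

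Several stronger readings are tempting and are not supported:

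- A reader might infer that the trial has no hierarchy at all. It has one: a single primary, with the rest labelled secondary. What is missing is an order among the secondary outcomes.
- A reader might infer a chance of about 13% of falsely claiming cognitive benefit. That figure counts differences in both directions and needs an assumed correlation near 0.5. In the favourable direction the same model gives 6.5%, against 2.5%.
- A reader might infer that a null blood pressure result could be replaced by any significant secondary. The article fixes its primary, and its Discussion speaks of a set of outcomes without saying that one suffices.
- A reader might extend the count to the cardiometabolic secondaries. They number 12 to 16, depending on how lipids and derived measures are counted. For 19 tests in all, the chance runs from 22% at correlation 0.8 to 62% at 0, which is too loose to support a figure.

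**Conclusion.** The concern holds for the cognitive scores and does not touch the primary outcome. If the diets have the same effect on cognition, at least one of the four scores will be significant in either direction about 10% to 16% of the time, with Total as the mean of three domains correlated 0.8 to 0; four independent scores give 18.5%. That is two to nearly four times the 5% of a single test. In the favourable direction the chance is about 5% to 8%, against 2.5%.

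These sizes rest on assumed correlations and an assumed make-up of Total, since the article gives neither. The direction does not depend on the assumed values: over the whole range examined, four undifferentiated tests exceed the error of one. This is worth correcting before analysis, but it does not threaten the trial's main result.

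**What to change.** In section 2.7, name Total Cognitive Functioning as the single key cognitive outcome. Test it at two-sided 0.05 as its own question, and state that it alone decides both the cognitive conclusion and whether the follow-on regression is done. State that Memory, Processing Speed, Executive Functioning and the other secondary outcomes are supportive, reported as estimates with 95% confidence intervals, and not adjusted for multiplicity. The sentence in section 3 should then rest on the primary and this key outcome.

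This returns the error rate for the cognitive conclusion to 5%. It costs only wording, with no extra participants or data, and leaves the power for Total unchanged. The small downside is that an effect confined to one domain could not by itself support a claim of significance. Formal testing of the domains with Holm would reopen that route, but with power of 0.72 at the first step it falls below the article's own target of 0.8. Making the cognitive test conditional on the blood pressure result is not needed, because cognition is a separate stated objective.
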